**1. Introduction and Problem Statement**

Currently, low back pain is one of the most common problems worldwide, with a prevalence rate of 80 to 85%, leading to disability throughout a person's life (1, 2). Among these individuals, 5 to 10% progress to chronic low back pain, which results in high treatment costs and significant pain and suffering (3). Low back pain has led to a restriction of approximately 39% of activities globally (4).

In general, chronic low back pain is defined as pain that persists for more than 3 to 6 months (5). Chronic pain is a complex syndrome that includes emotional, psychological, and mechanical components (6). Despite advancements in diagnostic tools and techniques, determining the exact cause of symptoms is often impossible. What is evident, however, is that in chronic conditions, treatment based solely on correcting structural abnormalities in the musculoskeletal system is often unsuccessful, indicating the presence of other pathophysiological and biopsychosocial mechanisms in chronic low back pain (1, 7).

For over 20 years, increasing research has shown that individuals with low back pain may have alterations in their central nervous system (8). Many pieces of evidence suggest that structural changes in the musculoskeletal system of the lower back may not be the sole contributors and that extensive reorganization in the cortex, such as neurochemical, functional, and structural disorders in the brain, could play a role in the persistence of low back pain. These changes need to be considered from a therapeutic perspective as well. In other words, addressing the pathophysiological mechanisms of chronic low back pain helps in identifying the most effective treatment methods for this group of individuals (7). Recent studies suggest that structural and functional changes in the central nervous system (9) of individuals with musculoskeletal pain reflect adaptive neurophysiological processes and contribute to repair processes by protecting structures. Laboratory and clinical findings indicate that these neurophysiological adaptations might become enduring and progressive, leaving chronic symptoms behind (10).

Indeed, this maladaptive plasticity in the central nervous system in response to pain is one of the most critical phenomena explaining why individuals with chronic low back pain respond poorly to traditional treatments (11). Neuroplasticity is a fundamental and intrinsic neurophysiological process involving structural, functional, and organizational changes in the brain and nervous system that continuously occur throughout an individual's life (10). The primary mechanism of neuroplasticity in the central nervous system involves functional or interference changes in the inherent properties of neurons as well as structural changes in the number or location of synapses between neurons (12). Plastic adaptation initially stems from musculoskeletal structural damage and results in experiencing pathophysiological conditions even without anatomical/structural musculoskeletal damage in chronic conditions (10). Synaptic plasticity involves enduring changes in synaptic quality due to synaptic strengthening or weakening (13).

Evidence indicates that pain is related to maladaptive plasticity in the sensory and motor cortices of the central nervous system (14, 15). These findings complement other behavioral evidence suggesting that there are issues in the sensory-motor function of the lower back in patients, which can ultimately lead to disability (1). Sensory-motor control of the lower back is considered one of the key factors in the progression and recurrence of low back pain (16).

Optimal sensory-motor behaviors depend on precise central processing and integration of sensory information into motor commands (16). There is a complex relationship between perception and action (1), with motor outputs generally depending on sensory inputs. These sensory inputs include somatosensory information about body position and movement and information from the proprioceptive network (8). Sensory information plays a crucial role in selecting the appropriate motor strategy to stabilize and move the spine (1). To maintain spinal posture and control movement, ongoing interaction between motor outputs of the neural pathways related to paraspinal muscles and sensory inputs, including proprioception, at various levels of the nervous system is essential (9, 17).

Overall, pain affects sensory-motor function. When pain occurs, muscle force production capacity decreases; muscular coordination is disrupted (18); body patterns during work change (7); proprioception is impaired (1, 16); tactile accuracy decreases (1, 7, 11, 16); and the ability to integrate sensory information into motor commands is reduced (18). In other words, disruption in sensory-motor control, which encompasses all sensory and motor processing, leading to muscle control and movement as well as maintaining spinal alignment and ultimately ensuring healthy function and appropriate loading of the spine, can be a potential underlying mechanism for the development or persistence of pain (8).

As mentioned earlier, one of the pathophysiological mechanisms proposed for the disruption in sensory-motor control in individuals with low back pain is changes in the sensory-motor processing of the central nervous system. Indeed, findings suggest that in individuals with chronic low back pain, reorganization of brain areas related to sensory information processing may be involved in sensory accuracy related to body perception and play a significant role in the neural control of the lumbar region (1). Overall, reorganization of the sensory-motor system in the brain may cause changes in sensory and motor manifestations, including disruptions in body perception (10) and functional changes in motor planning, ultimately leading to impaired postural control (1).

Regarding sensory processing, studies indicate that in individuals with low back pain (both acute and chronic phases), changes and disruptions occur in the primary sensory cortex (S1), and these changes are strongly associated with pain intensity, functional deficits, and symptom chronicity (11, 19). During acute conditions or experimental muscle pain, decreased excitability in S1 occurs before changes in motor output (19). Additionally, patients with decreased excitability in the S1 region experience more pain compared to those with increased excitability (19). In chronic pain, pain memory progression can alter the somatotopic map of S1 and lead to heightened sensitivity even without pain stimuli (12).

Furthermore, a significant correlation exists between gray matter density in the brain and pain intensity and duration (12). Recent evidence shows that chronic low back pain is associated with reduced gray matter in the somatosensory cortex (20). Other studies have indicated that in chronic low back pain, the thickness of the primary (S1) and secondary (S2) sensory cortices is reduced compared to the control group (11). The S1 region processes unisensory inputs and integrates them with motor signals to guide movement. The S2 region integrates multisensory and bilateral sensory inputs and is a key point in sensory-motor integration through its connections with motor areas (16). S1 also refines motor control (17). Studies have also shown that in individuals with low back pain, the S1 region, which receives information from the trunk, shifts its location in the brain, thereby disrupting its connection with M1 and reducing spinal motor control (11). Another study reported that in patients with chronic low back pain, the somatotopic representations in S1 shift by 2.5 cm, and changes in gray matter volume are associated with pain chronicity. Additionally, non-painful afferents are suppressed, and cortical excitability decreases (19). In another study, individuals with chronic low back pain who received painful intradermal electrical stimulation showed that the S1 region shifted inward compared to healthy individuals (1). Some studies have also shown that in chronic pain, decreased activity in S1 and S2 is accompanied by increased activity in the prefrontal cortex, indicating why emotional, motivational, and cognitive states are more pronounced in chronic pain (19). Studies suggest that S1 and the posterior-external part of the prefrontal cortex can function as two neural networks in motor planning, movement execution, motor control, and pain management (21).

Regarding motor processing, studies indicate that individuals with chronic low back pain exhibit decreased excitability in M1 compared to healthy individuals (6). Other studies show that these individuals experience decreased M1 excitability and reduced GABA receptor activity (11), and those with decreased M1 cortical excitability experience significantly more pain immediately after pain onset and have slower recovery compared to those with higher M1 excitability (19).

Other studies also support that paraspinal muscle excitability, including multifidus, is reduced in individuals with chronic low back pain (22, 23) and the motor cortex map of trunk muscles undergoes reorganization. These studies reveal a connection between cortical changes and pain intensity and motor control (24). Additionally, it has been reported that in these individuals, the M1 area related to transverse abdominis muscle control shifts outward and posteriorly, which is associated with delayed activation of the transverse abdominis during rapid shoulder flexion (23). This delay in abdominal muscle reflexes may cause instability in spinal stabilization (25). Other studies have shown that cortical representations of multifidus and transverse abdominis muscles in healthy individuals are asymmetric, but in individuals with chronic low back pain, representations of the transverse abdominis muscle are more symmetrical and located predominantly in the left motor cortex (26). Paraspinal muscles receive descending inputs from the motor cortex and corticospinal pathways. These pathways not only cooperate in voluntary activity but also play a crucial role in postural control. Human studies have shown that postural activity of the trunk during limb movements decreases when the motor cortex is inhibited (24). Cortical changes cause the paraspinal fascicles to lose separate functional activity and act collectively. In other words, these muscles lose their ability to control independently and differentially, leading to similar activity between the longissimus and multifidus muscles. Consequently, postural deficits arise. Findings indicate that patients with more than 6 months of low back pain have a reduced M1 map in both acute and chronic phases. The reduced volume related to paraspinal muscles reflects decreased motor cortex excitability. Consequently, decreased motor cortex excitability results in limitations in reactive and anticipatory movements, aimed at minimizing pain and preventing further injury (27). This mechanism may reduce pain in the short term but can increase structural stress, reduce movements over time, and alter motor patterns, contributing to the persistence of low back pain (28). Overall, altered motor function and changes in the central nervous system due to low back pain may lead to impairments in spinal control and contribute to its persistence and recurrence (6, 29).

**2. General Objective**

The impact of combining sensory-motor exercises with transcranial direct current stimulation (tDCS) on brain sensory-motor processing and clinical symptoms in individuals with chronic low back pain.

**3. Descriptive Objectives**

**Primary:**

- To determine the average level of lumbar movement control in the groups (intervention and control), before and after the intervention.
- To determine the average level of disability in the groups (intervention and control), before and after the intervention.
- To determine the average level of pain in the groups (intervention and control), before and after the intervention.

**Secondary:**

- To determine the average amplitude of N80 and N150 in the groups (intervention and control), before and after the intervention.
- To determine the average active motor threshold of the multifidus and transverse abdominis muscles in the groups (intervention and control), before and after the intervention.
- To determine the average amplitude of the motor-evoked potentials (MEPs) of the multifidus and transverse abdominis muscles in the groups (intervention and control), before and after the intervention.

**4. Analytical Objectives**

**Primary:**

- To compare the average level of lumbar movement control in the groups (intervention and control), between before and after the intervention.
- To compare the average level of lumbar movement control between the groups (intervention and control) before and after the intervention.
- To compare the average level of disability in the groups (intervention and control), between before and after the intervention.
- To compare the average level of disability between the groups (intervention and control) before and after the intervention.
- To compare the average level of pain in the groups (intervention and control), between before and after the intervention.
- To compare the average level of pain between the groups (intervention and control) before and after the intervention.

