**6. Practical Implications**

If combining exercises with tDCS yields better results, this method could be recommended for clinical use. If there is little difference between the treatment groups, it could be suggested that exercises alone are effective, thus avoiding additional costs, or seeking a new treatment method.

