**13. Sample Size**

The sample size was calculated using G*Power 3.1.3 software, based on the Jafarzadeh et al. study [28], with pain as the primary outcome measure. The calculation used a between-group Cohen's f of 0.473, a power of 0.8, and an α of 0.05. This power analysis indicated that at least 30 participants were needed. To account for a potential 15% dropout rate, 34 participants were recruited.

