**18. Data Analysis Method**

- All descriptive and statistical analyses will be conducted using SPSS software version 23.
- Descriptive statistics will include the calculation of measures of central tendency (mean) and dispersion (standard deviation).
- The Shapiro-Wilk test will be used to assess the normal distribution of the data.
- To compare baseline (pre-treatment) between the two treatment groups, an Independent t-test with a significance level of 0.05 will be used.
- To examine the effects of within-subject factors (time stages: pre- and post-treatment) and between-subject factors (type of treatment: real transcranial electrical stimulation with sensory-motor exercises vs. sham transcranial electrical stimulation with sensory-motor exercises), a Two-Way Mixed between-within ANOVA will be employed. Effect sizes will be reported using η², and interpreted as small (0.01), medium (0.06), and large (0.14).
- Pearson Correlation will be used to assess the relationship between clinical parameters and neurophysiological parameters related to sensory and motor cortical excitability.

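### For each primary outcome, within-arm and between-arm comparisons share primary rank, and the protocol never names the contrast that isolates tDCS as the deciding one

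*Protocol*

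**What the plan says.** Section 4 (Analytical Objectives, Primary) has two bullets for each of lumbar movement control, disability and pain. For pain they are "To compare the average level of pain in the groups (intervention and control), between before and after the intervention" and "To compare the average level of pain between the groups (intervention and control) before and after the intervention". Neither is ranked above the other. Section 5 repeats both kinds as research questions.

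Section 18 gives the model. It opens "To examine the effects of within-subject factors (time stages: pre- and post-treatment) and between-subject factors", identifies the latter as treatment type, and says that "a Two-Way Mixed between-within ANOVA will be employed". It does not mention an interaction, a group-by-time effect or a difference in change, and neither does any other section. For the arms before treatment, "an Independent t-test with a significance level of 0.05 will be used".

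Section 13 sizes the trial on pain: "The calculation used a between-group Cohen's f of 0.473, a power of 0.8, and an α of 0.05". It adds: "This power analysis indicated that at least 30 participants were needed". Section 6 draws the practical conclusion: "If combining exercises with tDCS yields better results, this method could be recommended for clinical use". It names no contrast.

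**The concern.** The trial asks what real tDCS adds to exercise. Under section 17-2 both arms do the same sensory-motor exercises, and section 14 requires pain of at least 4 at entry. Improvement within an arm, or a significant time effect, therefore mixes exercise, natural course and regression to the mean. It would be expected even if tDCS did nothing. The between-arm comparison before treatment tests nothing about treatment, because the arms are randomised.

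Three between-arm contrasts remain: the post-treatment difference, the group main effect and group-by-time. Each can be used to test tDCS, but they differ in power and can disagree on the same data. With none named as deciding, the conclusion can depend on which one is read after the results are known. The primary label on the within-arm comparisons also gives formal standing to results that cannot answer the question.

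**Working it through.** **Inputs.** From section 13: f = 0.473, α = 0.05, power 0.80, N = 30 (34 recruited). From section 17-2: two arms in balanced blocks, so 15 to 17 per arm. The documents give neither the pre-post correlation r nor the gain shared by both arms. These are assumptions: r = 0.5 with range 0.3 to 0.7, and a shared gain of 0 to 1.0 SD. Tests are taken as two-sided.

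**1. Which contrast gives N = 30?** For the group main effect over two measurements, the noncentrality is λ = f²·N·2/(1 + r).
- N = 30, r = 0.5: 0.473² × 30 × 2/1.5 = 8.95, power 0.823.
- N = 28: power 0.794.

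So 30 is reproduced as the group main effect. For the interaction with the same f, λ = f²·N·2/(1 − r), and 12 patients would suffice. A post-treatment comparison alone would need 38. On this reproduction, section 13 does not make group-by-time the deciding contrast either.

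**2. Power of each contrast.** Assume equal expected baselines and a post-treatment difference D = 2f = 0.946 SD, with n = 15 per arm and r = 0.5.

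| Contrast | Expected difference | Standard error | Ratio | Power |
|---|---|---|---|---|
| Group main effect (mean of pre and post) | D/2 = 0.473 | √[(2/15)(1 + r)/2] = 0.316 | 1.50 | 0.30 |
| Group-by-time (difference in change) | 0.946 | √[(2/15)·2(1 − r)] = 0.365 | 2.59 | 0.71 |
| Post-treatment adjusted for baseline (ANCOVA) | 0.946 | √[(2/15)(1 − r²)] = 0.316 | 2.99 | 0.82 |

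As r goes from 0.3 to 0.7, the powers run from 0.34 to 0.27, from 0.56 to 0.90, and from 0.75 to 0.94. The group main effect loses because half of what it averages was measured before treatment. For it to reach the 0.823 of step 1, the averaged difference must be 0.946 SD. With equal baselines that means a post-treatment difference of 2 × 0.946 = 1.892 SD.

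**3. False positives if any between-arm contrast may decide.** With no tDCS effect, each contrast alone has size 0.05. With equal variances before and after, the mean of the two scores and the change are uncorrelated, so for the group main effect or group-by-time the rate is about 1 − 0.95² = 0.0975. Simulation (15 or 17 per arm, r = 0.3 to 0.7) gives about 0.10. Adding the post-treatment comparison gives 0.11 to 0.12. These rates are per outcome and two-sided; about half would favour tDCS.

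**4. If the arms were tested separately.** Let p be the probability that an arm shows significant improvement. With no tDCS effect p is the same in both independent arms, so the real arm is significant and the sham arm is not with probability p(1 − p), which cannot exceed 0.25.

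| Per arm | r | Shared gain | p | p(1 − p) |
|---|---|---|---|---|
| 17 | 0.5 | 0 | 0.025 | 0.024 |
| 17 | 0.5 | 0.5 SD | 0.49 | 0.25 |
| 17 | 0.5 | 0.8 SD | 0.87 | 0.11 |
| 17 | 0.5 | 1.0 SD | 0.97 | 0.03 |
| 17 | 0.7 | 0.8 SD | 0.98 | 0.02 |
| 15 | 0.7 | 0.8 SD | 0.96 | 0.04 |

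The time main effect at N = 34 and r = 0.5 is significant in 81% of such trials at a shared gain of 0.5 SD, and in more than 99% at 0.8 SD.

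**The case against.** The best defence is that section 18 already fixes a suitable model. A two-way mixed ANOVA produces the group-by-time test, and naming the deciding term is often left to an SAP, which is not at hand. That holds for the missing name alone. It does not cover section 4, which itself ranks within-arm comparisons as primary. An SAP that made group-by-time decisive would then conflict with the protocol.

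Other parts of the defence stand and limit the point:

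- A reader might infer that the trial will claim benefit because the real arm improves significantly and the sham arm does not. Section 18 specifies no separate test in each arm. Its only t-test is the baseline one, and the within-arm objectives can be read as the ANOVA's time effect. The 25% in step 4 is a mathematical ceiling, not an expected rate.
- A reader might infer that the group main effect does not test tDCS. It does, with size 0.05 when taken alone. Its fault is low power. The post-treatment comparison is likewise a valid randomised test.
- A reader might infer that the false-positive rate is already inflated. The 0.10 to 0.12 needs a rule that accepts any significant between-arm contrast, and the protocol states no such rule.
- Section 6 goes on to consider little difference between the treatment groups, and section 13 uses a between-group effect. Both suggest that a between-arm comparison is intended, though neither says which.
- The baseline comparison has its own t-test in section 18 and is not offered there as evidence of efficacy.

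**Conclusion.** The point holds as a should-fix. Section 4 gives primary rank to comparisons that cannot test tDCS, and no section names the between-arm contrast that decides.

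The firmest consequence concerns power. The stated N = 30 reproduces as the group main effect at an assumed correlation of 0.5. For a post-treatment difference of 0.946 SD that contrast has power of about 0.30, against 0.71 for group-by-time and 0.82 for ANCOVA. Reading 2f as the post-treatment difference is also an assumption, because section 13 does not say how f was obtained.

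The error-rate consequences are conditional: about 0.10 to 0.12 per outcome if any significant between-arm contrast were accepted, and from below 5% to at most 25% if the arms were tested separately and only the real arm was significant. The documents commit the trial to neither practice, but their wording leaves room for both.

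**What to change.** - **Sections 4 and 18:** name one deciding between-arm contrast for each primary outcome, two-sided at 0.05 and reported with its 95% CI. The preferred choice is the post-treatment difference adjusted for baseline (ANCOVA). Otherwise use group-by-time, but not both: they are different estimators with different power, and allowing either would leave the choice open again.
- **Section 4:** move the within-arm and pre-treatment comparisons out of the primary objectives. State that these, the time effect and the group main effect are descriptive and will not support a claim for tDCS.
- **Section 6:** tie the recommendation to the chosen contrast.
- **Section 13:** state which contrast the 0.80 power refers to and the correlation assumed.

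The change is to wording and needs no new measurements. Within-arm improvement could no longer be reported as a primary result, and the stated power may change once it is tied to the chosen contrast.
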